#### Outcomes

The primary outcome for feasibility is recruitment defined by the ability to recruit FCPs and patients to the PRISM study. Secondary outcomes are detailed in table 1. Clinical behaviour metrics may vary based on the data collected by different services as part of their current data collection practice. A full list of clinical behaviour metrics is also listed in online supplemental appendix 2.

**Table 1 T1:** Primary and secondary outcomes for PRISM feasibility

Category	Outcome	Details/metrics	Timepoints
Primary outcome	Recruitment	Number of participants recruited	Baseline
Feasibility outcomes	Retention Data collection engagement Dashboard engagement Patient outcomes collection Clinician outcomes collection Supervision log FCP characteristics Missing data	FCPs and patients retained Number of FCP encounters, completeness and characteristics of data collection Logins (FCP/supervisor), time spent, pages visited Clinical activity data, PROMs (EQ-5D-5L, MSK-HQ, WPIA, global change), PREMs (GP Communication Scale of GPAQ)^42^ Manchester Scale of Supervision^43^ Monthly entries by FCP and supervisor Years qualified, band, WTE%, appointment length Frequency and %	3FU, 6FU (FCPs); 3FU (pts) Monthly Monthly Baseline, 3FU Baseline, 3FU, 6FU Monthly Baseline Baseline, 3FU (patients); Baseline, 3FU, 6FU (clinicians)
Clinical decision-making: investigations	MRI requests, X-ray, US, CT, bloods Referrals: social prescribing, health and well-being, vocational services, FitNote Referrals: specialist Physio/MSK/ESP MCATS, Podiatry, OT, Falls Referrals: Neuro, Ortho, Rheum Back to GP for medical reason, GP for prescription, GP for injection, GP for referral	Proportion of all patients	Monthly
Social norms outcomes	Individual outliers Team outliers	Proportion of outlier occurrences (≥20%) Overall outlier occurrence	Monthly
Supervision outcomes	Supervision log MCSS-26^26^	Participation and dashboard/guidebook use Manchester Scale of Clinical Supervision	Monthly Baseline, 3FU, 6FU
Patient outcomes	PREM PROM Pain site	GP Communication Scale EQ-5D-5L, Musculoskeletal Health Questionnaire,^44^ modified WPAI,^45^ Global Percieved Effect^46^ Body site	Baseline Baseline, 3FU Baseline, 3FU
Health economic outcomes	EQ-5D-5L Cost per intervention	Health-related quality of life Imaging, referrals, platform, training, time costs	Baseline, 3FU 6FU
Carbon reduction outcomes	CO_2_ emissions	MRI, X-ray, ultrasound, equipment, consumables, waste, mobility, infrastructure	6FU

EQ-5D-5L, EuroQol 5-Dimension 5-Level; ESP, Extended Scope Practitioner; FCP, First Contact Physiotherapist; FU, follow up; GPAQ, Global Physical Activity Questionnaire; MCATS, Musculoskeletal Clinical Assessment and Treatment Service; MCSS-26, Manchester Clinical Supervision Scale (26-item version); MSk, musculoskeletal; PREM, patient-rated experience measure; PROM, patient-rated outcome measure; WPIA, Work Productivity and Activity Impairment.

#### Sample size

We will recruit from four sites with approximately 8–12 physiotherapists per site. Primary care areas will be allocated on a 1:1 basis. Four sites have been selected as these are the numbers that are feasible to work within the available timeframe.

For patient participants: It is expected that eight physiotherapists per site will see at least 10 patients per week. This is 80 patients per site per week and 320 patients per week across four sites. Over 3 months this will mean 3840 patients will be invited to take part in the study. If 5% respond we will have 192 patients. If 10% respond 384 patients

An estimate of the recruitment period for the trial is 3 months calculated based on the expected number of eligible sites and the time taken to assess against the inclusion/exclusion criteria. We aim to recruit 4 sites in 4 weeks.

#### Statistical analysis

This protocol is reported in line with the Standard Protocol Items: Recommendations for Interventional Trials (SPIRIT) guidelines for reporting outcomes in trial protocols.^32^ It is not possible to blind FCPs to the intervention arm. Patients will be blinded to the intervention arm. The statistician and health economist will be blinded to the randomisation in line with clinical trials unit protocols.

Analysis will be done using intention-to-treat principles based on clusters. Categorical measures will be summarised using frequencies and percentages. Continuous measures will be summarised using means and SD or medians and IQRs depending on distribution. All outcome measures will be summarised separately by study arm. Potential therapist effect will be assessed using the intraclass correlation coefficient. The precision of estimates will be assessed using 95% CIs. We will look at missing data on key variables in the primary or secondary outcomes as this is a feasibility outcome.

#### Economic evaluation

The analysis will focus on the feasibility of collecting data that would inform an economic evaluation in a full trial. We will also assess the feasibility of calculating the cost of the new dashboard in relation to any additional training or delivery resources or additional physiotherapy time will also be calculated. The feasibility of collecting Quality Adjusted Life Years (QALYs) over 6 months will be calculated from patient responses to questionnaires. We will report rates of missing data, mean utility scores and SD at each follow-up time point. QALYs are used in determining the additional value of a new healthcare intervention compared with current practice.^33
34^ The second component will be the feasibility of collecting resource use data to apply published unit costs to.^35
36^ Descriptive statistics will be reported for each resource per physiotherapy intervention. The average cost per patient will be calculated to evaluate any potential cost-savings from the new dashboard as a result in changes in decision-making practice.

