#### Trial duration

The expected duration of the trial is 7 months for sites/FCPs from baseline to 6 months follow-up, allowing for data collection to begin 1 month before baseline outcomes are taken. The duration of the trial for patients is 3 months from baseline to final follow-up at 3 months. The end of trial is the last follow-up completion of the last participating FCP patient and FCP.

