### Data collection and data analysis

#### Data collection

Patients will be texted by their GP practice about the study. If they click the link to participate, patients will submit demographic details (name, age, ethnicity) which we will use for research analysis and complete outcome and experience measures (PROMs and PREMs) digitally, via a link to REDCap. Follow-up measures will be sent by text after 3 months.

FCPs and supervisors will keep digital logs of supervision sessions and engagement with the dashboard. This will also be recorded on REDCap and a link will be emailed to them on a monthly basis. PRISM dashboard usage (logins) will also be recorded. Trial data are stored on a secure server in the Clinical Trials Unit behind the University College London firewall.

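### The economic section sets a 6-month QALY horizon, but patient EQ-5D-5L is scheduled only at baseline and 3 months

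*Protocol article*

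**What the plan says.** On the QALY horizon, the protocol article says under Economic evaluation: "The feasibility of collecting Quality Adjusted Life Years (QALYs) over 6 months will be calculated from patient responses to questionnaires". The same paragraph promises missing-data rates and mean utilities with SD at follow-up.

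On patient timing, four places agree with each other:

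- Trial duration: "The duration of the trial for patients is 3 months from baseline to final follow-up at 3 months".
- Data collection: "Follow-up measures will be sent by text after 3 months". No later patient questionnaire is described.
- Outcomes, Table 1, retention row: "3FU, 6FU (FCPs); 3FU (pts"), and missing-data row: "Baseline, 3FU (patients); Baseline, 3FU, 6FU (clinicians"). Both separate patients from clinicians and give 6FU only to the latter.
- Outcomes, Table 1, patient-outcome and health-economic rows: EQ-5D-5L at baseline and 3FU.

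The 6-month point belongs to another level of the trial. Trial duration says: "The expected duration of the trial is 7 months for sites/FCPs from baseline to 6 months follow-up". Table 1 also places the cost item ("Imaging, referrals, platform, training, time costs") and the carbon outcomes at 6FU.

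**The concern.** A QALY over a period needs utility measured, or explicitly modelled, across that whole period. Here the horizon is tied to patient questionnaires and runs to month 6, while the last patient questionnaire is at month 3. As written, the output cannot be produced from observed data.

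What is at stake is modest but specific. The section exists to show whether the data for a later economic evaluation can be collected. Completion and variability of EQ-5D-5L at 6 months are what a later study with a 6-month horizon would want to know, and this schedule cannot supply them. If the sentence stands, 3-month completion may be reported as evidence about 6-month collection, or an unplanned extrapolation may fill the gap.

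**Working it through.** **Inputs, all from the protocol article**

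- Stated QALY horizon: 6 months = 0.50 years (Economic evaluation).
- Last patient EQ-5D-5L: 3 months = 0.25 years (Trial duration; Data collection; Table 1).
- Expected patients: 192 at 5% response, 384 at 10% (Sample size).

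**1. The plan's own count.** 8 FCPs × 10 patients × 4 sites × 12 weeks = 3840 invited; 3840 × 0.05 = 192; 3840 × 0.10 = 384. All three figures reproduce.

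**2. Share of the horizon observed.** 3 / 6 = 50%. The number of patients with a scheduled 6-month EQ-5D-5L is 0 of the 192 to 384 expected.

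**3. What the schedule can deliver.** With U0 and U3 the utilities at baseline and 3 months, and the trapezoid rule:

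QALY(3 months) = 0.25 × (U0 + U3) / 2

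At full health (U0 = U3 = 1) this is 0.25. Full health over 6 months would give 0.50.

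**4. What a 6-month figure would need.**

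QALY(6 months) = 0.25 × (U0 + U3) / 2 + 0.25 × (U3 + U6) / 2

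U6 is not scheduled for anyone, so the second term depends on an assumption.

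**5. Illustration with assumed utilities.** The documents give no utilities. Take U0 = 0.60 and U3 = 0.70 purely as an example.

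- Observed 3-month QALY: 0.25 × (0.60 + 0.70) / 2 = 0.1625.
- Month-3 utility carried forward (U6 = 0.70): 0.1625 + 0.25 × 0.70 = 0.3375.
- Return to baseline by month 6 (U6 = 0.60): 0.1625 + 0.25 × (0.70 + 0.60) / 2 = 0.3250.

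The two conventions differ by 0.3375 − 0.3250 = 0.0125 QALY in this example. About half of either total (0.1750 of 0.3375, or 0.1625 of 0.3250) is assumed and not measured.

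**6. Alternative readings of the 6 months.** It might mean the FCP follow-up period, or the calendar span of about 3 months of recruitment plus 3 months of follow-up. The sentence says neither. Under both readings each patient still contributes only 3 months of utility, so the stated horizon would still be wrong for a patient-level QALY.

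**The case against.** The strongest reply is that this is one phrase out of line in an otherwise consistent schedule. The trial is a feasibility study with recruitment as its primary outcome. No hypothesis test, sample size or cost-effectiveness ratio in the article uses a QALY total. EQ-5D-5L at baseline and 3FU can be collected as planned, and its missing data, means and SDs can be reported. All of that stands, and it limits the severity. It does not remove the conflict, because the article states a horizon that its own patient schedule does not reach.

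A second reply is that the full schedule of events (online supplemental appendix 3) is not shown and might settle the matter. It could show which figure is the slip. If it listed a 6-month patient EQ-5D-5L, however, it would contradict Trial duration, Data collection and Table 1, so reconciliation would still be needed.

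A reader might also infer several stronger points that the article does not support:

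- *That no QALY can be collected.* A 3-month QALY can be; only the 6-month horizon fails.
- *That the promise of utilities at every follow-up point is a second contradiction.* This is generic wording, which a single follow-up satisfies.
- *That Table 1 already shows clashing cost and QALY horizons.* The cost row includes platform, training and time costs, which are delivery-level items. 6FU may only mark when costs are assembled at the end of the FCP period.
- *That the future full trial would inherit mismatched horizons.* Its horizon is not set here; this study only informs that protocol.

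**Conclusion.** The inconsistency is real and nothing in the article resolves it. Half of the stated QALY horizon (0.25 of 0.50 years) is unobserved for every patient, and a 6-month value would require an extrapolation that is not planned. The effect is confined to a secondary feasibility output. This is a should-fix correction of an internal inconsistency; the results that the trial is mainly designed to give are not threatened.

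The conclusion assumes that the patient schedule in the article is the operative one, which its agreement across Trial duration, Data collection and Table 1 supports. The utilities in the illustration are assumed and carry no weight in the conclusion.

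**What to change.** Under Economic evaluation, replace the 6-month horizon with QALYs over 3 months, calculated as the area under the utility curve from baseline to 3FU, and state that utilities and missing data will be reported at baseline and 3FU. Add a note to Table 1 that the 6FU cost entry covers an FCP or service-level window, different from that of the patient QALYs. This is a wording change in the protocol and any health economics plan. It needs no new data; the price is a shorter stated horizon.

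The article does not say which figure was intended. If it was 6 months, Trial duration, Data collection and Table 1 must be brought into line by adding a 6-month patient EQ-5D-5L, with matching changes to consent and follow-up wording. That costs an extra contact per patient and must be decided before patient follow-up closes, because a 6-month response that was never requested cannot be recovered later.

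The correction should not go further and promise patient-level costs over the same 3 months as if they were already available. FCP activity data are fully anonymised before transfer, patient questionnaires sit separately in REDCap, and no linkage between the two is described.

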#### Carbon reduction analysis

This analysis will sit alongside the health economic analysis to measure CO_2_ emissions and ‘carbon unit costs’.^36^ The NHS and National Institute for Health and Care Research (NIHR) have a strategy for carbon reduction.^37
38^ Research has demonstrated methods for scalable carbon reduction in Primary Care^39^ CO_2_ emission measurements for commonly used healthcare modes such as MRI or X-ray are available.^40^ Recent analysis of MSK workflow in primary care has mapped carbon-related costs using a cost and carbon calculator which will be useful for this study.^41^ This research will aim to identify the feasibility of collecting the relevant data for carbon reduction analysis in a future trial that focuses on FCP workflow.

### Trial management and PPI

#### Trial Management Group

The Trial Management Group (TMG) will include the Chief Investigator, trial manager, health economist, data manager and statistician. The TMG will be responsible for overseeing the trial. The group will meet four times during the study and will send updates to PIs at each site. We will also have a Trial Steering Committee (TSC), the role of which is to provide overall supervision of the trial. The TSC will also take on the function of data monitoring committee as this feasibility trial does not require a separate data monitoring committee. The TSC will include patient and public involvement (PPI) members. consider relevant information, recommend any appropriate amendments/actions for the trial as necessary.

#### Patient and public involvement

PPI representatives engaged via Healthwatch and UCL were actively engaged from the outset, contributing to the design of the research, the development of the intervention and the creation of participant-facing materials. Healthwatch PPI members provided valuable insights into patient priorities, acceptability of recruitment and consent. UCL-based PPI contributors worked closely with the research team to create patient facing documentation and to refine the dashboard and guidebook, ensuring these tools were accessible and relevant to patients’ needs. PPI representatives also participated in the qualitative work package that informed the intervention’s content and structure. Throughout the trial, a PPI member will sit on the Trial Management Group, where they help oversee trial conduct, review recruitment and safety data, and ensure that patient and public perspectives remain integral to decision-making and dissemination. This collaborative approach ensures the study remains grounded in the experiences and priorities of those it is designed to benefit.

### Ethics and dissemination

To maximise reach and impact, dissemination will adopt a multi-modal approach. Alongside publication in high-impact, open-access journals and presentations at national and international conferences, we will leverage digital platforms to engage diverse stakeholders. Infographics summarising key findings will be hosted on institutional websites and shared via professional networks such as the CSP and FCP and digital forums. Social media campaigns using concise visual narratives will target clinicians and policymakers, amplifying engagement through LinkedIn and X ensuring PRISM’s insights inform practice and policy at scale. PPI partners will co-create accessible summaries to ensure findings resonate with service users and community groups.
